# **DISSEMINATION OF RESULTS**

A clinical study report containing the results of this trial will be made available to anyone who requests a copy; it will not include any patient-identifiable information.

A description of this clinical trial will be available on the Kenya Pharmacy and Poison’s Board clinical trial registry as required by Kenyan law, and with the Pan African Clinical Trials Registry.

# **POST TRIAL ACCESS**

In the event the study shows benefit, in consultation with regulatory authorities, an approximate cost package will be developed at AKUHN for treatment of Covid-19 pneumonia. In addition, AKUHN investigators will train and assist colleagues at other RT units in Kenya to adopt this treatment. The protocol used at AKUHN will be shared with the respective investigators.

# **BUDGET**

LDRT will be the only aspect of medical management that will experimental and beyond best practice of Covid 19 management. The cost for LDRT will be borne by the Department of Haematology- Oncology. The cost for PPE to be used for transportation to and from the RT unit and for the RT personnel will be borne by AKUHN.
“Special labs” will be drawn, processed and stored for future analysis and not bill to the patient. Patients will not be billed for any expenses related to the experimental treatment; this includes treatment expenses for adverse events that are related to the experimental treatment. All other charges are part of routine care of Covid 19 patients and will be billed to 3rd party or the patient, accordingly.

| **Item** | **Unit Cost Ksh** |
| --- | --- |
| PPE used during LDRT* | Ksh6,800 |
| Routine standard of are labs | Ksh24,100 |
| Urine pregnancy test* | Ksh1,500 |
| Special labs* | Ksh2,000 |
| Radiotherapy* | Ksh9,400 |

| **Personnel** | **Total Study Cost (Ksh)** |
| --- | --- |
| Data Management* | Ksh11,000 |
| Nurse* | Ksh33,188 |
| Investigator* | Ksh117,000 |
| Regulatory/monitoring* | Ksh69,750 |

| **Regulatory Items** | **Unit Cost Ksh** |
| --- | --- |
| PPB (one-time)* | Ksh100,000 |
| NACOSTI (annual)* | Ksh20,000 |

*the cost of these study related tests will be borne by the institution.

# **APPENDICES**

1. Informed consent form (English)
2. Informed Consent form (Swahili)
3. AKUH, N Inpatient COVID 19 management protocol
4. Case Report Form

# ***Appendix (iii)*** *AKUH, N Inpatient COVID 19 management protocol*

# ***Appendix (iv)*** *Case Report Form*

|  | **PATIENT DEMOGRAPHICS** | | | | | | | | | | | | | | | | | | | | | | | |  | | |  | | |  | | |  | | |  | | |  | | |  | | | | |  | | | | |  | |  | |  | |  | |  | |  | |  | |  |  |  |  |  |  |  |
| --- | --- | --- | --- | --- | --- | --- | --- | --- | --- | --- | --- | --- | --- | --- | --- | --- | --- | --- | --- | --- | --- | --- | --- | --- | --- | --- | --- | --- | --- | --- | --- | --- | --- | --- | --- | --- | --- | --- | --- | --- | --- | --- | --- | --- | --- | --- | --- | --- | --- | --- | --- | --- | --- | --- | --- | --- | --- | --- | --- | --- | --- | --- | --- | --- | --- | --- | --- | --- | --- | --- | --- | --- | --- |
|  |  | |  | |  |  |  |  |  |  |  |  | |  | | | | | | | | | | | D | | | D | | | M | | | M | | | Y | | | Y | | | Y | | | | | Y | | | | |  | |  | |  | |  | |  | |  | |  | |  |  |  |  |  |  |  |
|  | **Day month and year of birth** | | | | | | | | | |  |  | |  | | | | | | | | | | |  | | |  | | |  | | |  | | |  | | |  | | |  | | | | |  | | | | |  | |  | |  | |  | |  | |  | |  | |  |  |  |  |  |  |  |
|  |  | |  | |  |  |  |  |  |  |  |  | |  | | | | | | | | | | |  | | |  | | |  | | |  | | |  | | |  | | |  | | | | |  | | | | |  | |  | |  | |  | |  | |  | |  | |  |  |  |  |  |  |  |
|  | **Age** | |  | |  |  | YEARS | |  |  |  |  | |  | | | | | | | | | | |  | | |  | | |  | | |  | | |  | | |  | | |  | | | | |  | | | | |  | |  | |  | |  | |  | |  | |  | |  |  |  |  |  |  |  |
|  |  | |  | |  |  |  |  |  |  |  |  | |  | | | | | | | | | | |  | | |  | | |  | | |  | | |  | | |  | | |  | | | | |  | | | | |  | |  | |  | |  | |  | |  | |  | |  |  |  |  |  |  |  |
|  | **Sex** | |  | | Male …………. | | | 1 |  |  |  |  | |  | | | | | | | | | | |  | | |  | | |  | | |  | | |  | | |  | | |  | | | | |  | | | | |  | |  | |  | |  | |  | |  | |  | |  |  |  |  |  |  |  |
|  |  | |  | | Female…………………… | | | 2 |  |  |  |  | |  | | | | | | | | | | |  | | |  | | |  | | |  | | |  | | |  | | |  | | | | |  | | | | |  | |  | |  | |  | |  | |  | |  | |  |  |  |  |  |  |  |
|  |  | **Race** | | (Check Appropriate Option) | | | | | | | | |  | | |  | |  | |  | |  | |  | | |  | | |  | | |  | | |  | | |  | | |  | | |  | |  | | |  | |  | |  | |  | |  | |  | |  | |  | |  |  |  |  |  |  |  |  |
|  | Black African………………………………………………………………. | | | | | | | | | | | | | | 1 | |  | |  | |  | |  | | |  | | |  | | |  | | |  | | |  | | |  | | |  | |  | | |  | |  | | |  | |  | |  | |  | | | | | | | | | | | | | |
|  | Asian……………………………………………………………………………………………….. | | | | | | | | | | | | | | 2 | |  | |  | |  | |  | | |  | | |  | | |  | | |  | | |  | | |  | | |  | |  | | |  | |  | | |  | |  | |  | |  |  |  |  |  |  |  |  |  |  |  |  |  |  |
|  | Caucasian……………………………………………………………………………………………. | | | | | | | | | | | | | | 3 | |  | |  | |  | |  | | |  | | |  | | |  | | |  | | |  | | |  | | |  | |  | | |  | |  | | |  | |  | |  | |  |  |  |  |  |  |  |  |  |  |  |  |  |  |
|  | Unknown……………………………………………………………. | | | | | | | | | | | | | | 4 | |  | |  | |  | |  | | |  | | |  | | |  | | |  | | |  | | |  | | |  | |  | | |  | |  | | |  | |  | |  | |  |  |  |  |  |  |  |  |  |  |  |  |  |  |

|  | **Smoking history** | | | |  | Never |  | 1 |  |  |  |  |  |  |  |  |  |  |  |  |  |  |  |  |  |  |  |  |  |  |  |  |
| --- | --- | --- | --- | --- | --- | --- | --- | --- | --- | --- | --- | --- | --- | --- | --- | --- | --- | --- | --- | --- | --- | --- | --- | --- | --- | --- | --- | --- | --- | --- | --- | --- |
|  |  |  |  |  |  | Current | | 2 |  |  |  |  |  |  |  |  |  |  |  |  |  |  |  |  |  |  |  |  |  |  |  |  |
|  |  |  |  |  |  | Former | | 3 |  |  |  |  |  |  |  |  |  |  |  |  |  |  |  |  |  |  |  |  |  |  |  |  |

| **If current or former user, specify below.** | | | | | | | | Otherwise, N/A | | |  |  | |  |  |  |  |  |  |  |  |  |  |  |  |  |  |  |  |  |  |  |  |  |  |  |
| --- | --- | --- | --- | --- | --- | --- | --- | --- | --- | --- | --- | --- | --- | --- | --- | --- | --- | --- | --- | --- | --- | --- | --- | --- | --- | --- | --- | --- | --- | --- | --- | --- | --- | --- | --- | --- |
|  | Month and year subject last smoked | | | | | | | | | | | | M | M | M | Y | Y | Y | Y |  |  |  |  | | | |  |  |  |  |  |  |  |  |  |  |
|  |  | | | | | | | | | | | | |  |  |  |  |  | |  |  |  |  |  |  |  |  |  |  |  |  |  |  |  |  |  |
|  | Total number of years subject smoked | | | | | | | | | | | | |  |  |  |  | Years | |  |  |  |  |  |  |  |  |  |  |  |  |  |  |  |  |  |
|  |  |  |  |  |  |  |  |  |  |  | | |  |  |  |  |  |  |  |  |  |  |  |  |  |  |  |  |  |  |  |  |  |  |  |  |
|  |  |  |  |  |  |  |  |  |  | YES…. | | |  |  |  |  | | |  | 1 |  |  |  |  |  |  |  |  |  |  |  |  |  |  |  |  |
|  | Does subject use e-cigarettes? | | | | | | | | | NO | | |  |  |  |  | | |  | 2 |  |  |  |  |  |  |  |  |  |  |  |  |  |  |  |  |
|  |  |  |  |  |  |  |  |  |  |  | | |  |  |  |  |  |  |  |  |  |  |  |  |  |  |  |  |  |  |  |  |  |  |  |  |
|  |  |  |  |  |  |  |  |  |  |  | | |  |  |  |  |  |  |  |  |  |  |  |  |  |  |  |  |  |  |  |  |  |  |  |  |

| Physical Examination at Baseline | | | | | | | | | | |
| --- | --- | --- | --- | --- | --- | --- | --- | --- | --- | --- |
| (Please tick) | | | | | | | | | | |
| Code | System | Normal | Abnormal | N/A |  | Code | System | Normal | Abnormal | N/A |
| 1 | Cardiovascular |  |  |  |  | 9 | Neoplasia |  |  |  |
| 2 | Respiratory |  |  |  |  | 10 | Neurological |  |  |  |
| 3 | Hepato-biliary |  |  |  |  | 11 | Psychological |  |  |  |
| 4 | Gastro-intestinal |  |  |  |  | 12 | Immunological |  |  |  |
| 5 | Genito-urinary |  |  |  |  | 13 | Dermatological |  |  |  |
| 6 | Endocrine |  |  |  |  | 14 | Allergies |  |  |  |
| 7 | Haematological |  |  |  |  | 15 | Eyes, ear, nose, throat |  |  |  |
| 8 | Musculo-skeletal |  |  |  |  | 00 | Other_____________ |  |  |  |

If ***abnormal*** for any of the above, give further details on the Baseline Conditions/AE Log. Use a separate line for each condition.

Comments: ____________________________________________________________________

______________________________________________________________________________

______________________________________________________________________________

Investigator: **______________ _____________________ ___________________**­­

Name Signature Date

| D | D | M | M | M | Y | Y | Y | Y |
| --- | --- | --- | --- | --- | --- | --- | --- | --- |

Date of first COVID-19 symptoms

Symptoms at time of diagnosis

| **Symptoms at time of diagnosis** | **YES** | **NO** |
| --- | --- | --- |
| Fever |  |  |
| Chills |  |  |
| Repeated shaking with chills |  |  |
| Cough |  |  |
| Persistent pain or pressure in chest |  |  |
| Shortness of breath or trouble breathing |  |  |
| GI symptoms (e.g., diarrhea, nausea, loss of appetite) |  |  |
| Loss of taste or smell |  |  |
| Sore throat |  |  |
| Headache |  |  |
| Fatigue |  |  |
| Confusion or inability to arouse |  |  |
| Muscle Pain |  |  |
| Bluish lips or face |  |  |
| Other, if other specify: ______________________ |  |  |
| Other, if other specify: ______________________ |  |  |

| **Targeted Medical History and Baseline conditions log**  **(Please tick)** | | | | | |
| --- | --- | --- | --- | --- | --- |
|  | **Medical Condition** | **Absent** | **Present** | **Start Date**  **(if present)** | **Stop Date**  **(if present) or**  **✔ if ongoing and add to Baseline/AE Log** |
| 1 | Diabetes |  |  |  |  |
| 2 | Hypertension |  |  |  |  |
| 3 | Hyperlipidemia |  |  |  |  |
| 4 | Asthma |  |  |  |  |
| 5 | COPD |  |  |  |  |
| 6 | Obesity |  |  |  |  |
| 7 | Myocardial Infarction |  |  |  |  |
| 8 | Atrial fibrillation |  |  |  |  |
| 9 | Stroke |  |  |  |  |
| 10 | Diverticulitis |  |  |  |  |
| 11 | GI Perforation |  |  |  |  |

| General Medical History and Baseline Conditions *other than those above* | | | | | | | | |
| --- | --- | --- | --- | --- | --- | --- | --- | --- |
| **Does the subject have any other medical history or baseline conditions? YES**    **NO** | | | | | | | | |
| Code | System | *Yes | No |  | Code | System | *Yes | No |
| 1 | Cardiovascular |  |  |  | 9 | Neoplasia |  |  |
| 2 | Respiratory |  |  |  | 10 | Neurological |  |  |
| 3 | Hepato-biliary |  |  |  | 11 | Psychological |  |  |
| 4 | Gastro-intestinal |  |  |  | 12 | Immunological |  |  |
| 5 | Genito-urinary |  |  |  | 13 | Dermatological |  |  |
| 6 | Endocrine |  |  |  | 14 | Allergies |  |  |
| 7 | Haematological |  |  |  | 15 | Eyes, ear, nose, throat |  |  |
| 8 | Musculo-skeletal |  |  |  | 00 | Other __________________ |  |  |

| **Surgery and Procedure History** |
| --- |
| Has the subject had ant relevant surgeries or procedure? YES  NO  If Yes,   \| **Surgery of procedure description** \| **Surgery or procedure date** \| \| --- \| --- \| \|  \|  \| \|  \|  \| \|  \|  \| \|  \|  \| \|  \|  \| \|  \|  \| \|  \|  \| \|  \|  \| \|  \|  \| \|  \|  \| \|  \|  \| |

**Baseline Conditions & Adverse Event Tracking Log *Check box if there were no adverse events to be recorded* 🞏**

| Date Reported | Adverse Event Description | Serious  (Y or N) | Start Date  **& Time** | End Date **& Time**  or ✔ if ongoing | Grade (CTCAE v.5) | Severity^2^ | Outcome^1^ | AE Treatment^3^ | Study Attribution^5^ | Action Taken**^4^** | Drug Attribution^5^^ | PI Initials | Date of PI Initials |
| --- | --- | --- | --- | --- | --- | --- | --- | --- | --- | --- | --- | --- | --- |
|  |  |  |  |  |  |  |  |  |  |  |  |  |  |
|  |  |  |  |  |  |  |  |  |  |  |  |  |  |
|  |  |  |  |  |  |  |  |  |  |  |  |  |  |
|  |  |  |  |  |  |  |  |  |  |  |  |  |  |

# - AE number. “1” indicates the first adverse event documented on the form, 2 = the second, etc. If the adverse event changes in severity, enter it as a separate adverse event row on the paper form using the same AE number as the one that ended.

| **Outcome^1^** | **Severity^2^** | **AE Treatment^3^** | **Action Taken^4^ with Study Intervention** | **Attribution/  Relatedness^5^** |
| --- | --- | --- | --- | --- |
|  | 1 – Mild |  | 1 – Interrupted | 1 – Definite |
| 1 – Not recovered/not resolved | 2 – Moderate | 1 – Medication(s) | 2 – Discontinued | 2 – Probable |
| 2 – Recovered w/sequelae | 3 – Severe | 2 – Non-medication TX | 3 – Dose reduced | 3 – Possible |
| 3 – Recovered w/o sequelae |  | 3 – None | 4 – Dose increased | 4 – Unlikely |
| 4 – Recovering/Resolving |  |  | 5 – Not Applicable | 5 – Unrelated |
| 5 – Fatal |  |  | 0 – None | 6 – Not Applicable (did not receive intervention) |

**Fertility Status Form**

**Female Fertility Status**

| Age: _________ | Reseponse |
| --- | --- |
| 1. Is the patient breastfeeding? | NO  YES |
| 1. child bearing potential? |  |
| 1. Post menopaUsal?   If yes, indicate date of Last Menstrual period (must be at least 12 months prior) and add to medical history and skip remaining questions. | NO  YES, Date of last menstrual  period: _____________ |
| 1. surgical procedures? if yes, indicate date and type (removal of ovaries, fallopian tubes, and/or uterus). add to medical history and skip remaining questions. | NO  YES, Date of procedure: _____________ |
| 1. Are you on any birth control? (Yes or No) If yes, indicate TYPE (oral hormonal contraceptive, injectable, implant, barrier, etc.) and start date.   add to concomittant medications. | NO  YES |
| 1. patient agrees to remain on birth control throughout the study and for 3 months after the last dose. |  |
| or  patient agrees to abstain from heterosexual sex throughout the study and for 3 months after the last dose. |  |

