| Description of sites/facilities enrolling patients: | 1. AKUHN – a collaborative effort of the Clinical Research Unit, Dept. of Haematology-Oncology (radiation therapy section), infectious diseases, critical care |
| Description of study intervention: | 1. Single dose of 100 cGy LDRT administered to both lungs within 48h of determining eligibility 2. Cohort 1 : 5 patients will be treated. If acute treatment related SAE is observed in ≤1 of 5 patients, additional 5 patients will be treated. 3. Cohort 2 : 5 patients will be treated. If acute treatment related SAE is observed in ≤1 of 5 patients, additional 5 patients will be treated.   If > 1 of the initial 5 patients in either cohort experiences acute treatment related SAE, enrollment to that cohort will be halted. |
| Study Duration: | 3 months |
| Participant duration: | 28d from enrollment |

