# **End of study definition**

All eligible patients following consent will receive a single dose of LDRT within 48h of meeting eligibility and being enrolled on the study. Patients will undergo routine physical examination, vital signs and oxygenation parameters on a daily basis as part of standard of care. Observation period for the study will end on day 28 or at the time of discharge (or death), whichever comes first.

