# **ADVERSE EVENTS**

According to ICH Guideline for Good Clinical Practice, and for the purpose of this protocol, an adverse event is defined as any untoward medical occurrence in a clinical investigation subject administered pharmaceutical product, regardless of causal attribution. An adverse event can therefore be any of the following:

- Any unfavourable and unintended sign, symptom, or disease temporarily associated with these of a medicinal product whether or not considered related to the medicinal product.
- Any new disease or exacerbation of an existing disease (worsening in the character, frequency, or severity of a known condition)
- Recurrence of an intermittent medical condition not present at baseline.
- Any deterioration in a laboratory value or other clinical test that is associated with symptoms or leads to a change in the study treatment or concomitant treatment or discontinuation from Study drug.
- Adverse events that are related to protocol-mandated intervention, including those that occur prior to assignment of study treatment. (e.g. Screening invasive procedures)

A Serious Adverse Event (SAE) is any adverse event that meets any of the following criteria:

- Is Fatal
- Is Life threatening
- Requires of Prolongs inpatient hospitalization
- Is a congenital anomaly/birth defect in a neonate/infant born to a mother exposed to study drug/agent.
- Results in disability or permanent damage.

In this study all adverse events and Serious adverse events will be documented and assessed for treatment relation. The Radiation Therapy Oncology Group (RTOG) grading scale will be used to grade both acute and late toxicities; NCI CTCTAE 5.0 may be used for non-radiation related AEs. Pregnancy reporting will begin with first dose of LDRT through 6 months post-dose. The DSMC will be alerted in the event of an SAE and will meet within 24 hours. The adjudicating of the SAE causality will be performed jointly in consensus by the Principal Investigator and the DSMC.

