# **Exclusion Criteria**

1. Pre-existing lung comorbidity such as severe COPD, severe uncontrolled asthma or heart failure or concomitant active systemic infection.
2. Pre-existing dependency on supplemental oxygen prior to diagnosis of Covid 19 pneumonia
3. Patients on mechanical ventilation requiring 100% FIO2 and > 8mm PEEP to maintain SpO2 > 94% will not be eligible
4. Unwilling or unable to following protocol procedures
5. Pregnant and/or planned to be pregnant within in next 6 months
6. Hemodynamic and Ventilatory instability precluding transfer to Radiation Oncology department
7. Participation in another clinical trial involving an investigational product.

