# Discharge

If participant’s hospital stay is less than 28 days. If participant is discharged prior to Day 14, then monitoring for safety (Adverse Events, Concomitant Medications) will continue through Day 14:

- - Ordinal Score
  - Vital Signs and Oxygenation
  - Physical exam
  - Routine labs
  - Special labs (stored)
  - Pre-dose radiograph (Chest CT/X-Ray), per investigator discretion using the same modality as Screening, if possible
  - Adverse Events
  - Concomitant Medications

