**Specific details on procedures are as follows:**

1. **Ordinal Score (on a scale of 1-7) will be determined according to the following criteria:**

1: Discharged (or “ready for discharge” as evidenced by normal body temperature and respiratory rate, and stable oxygen saturation on ambient air or ≤2L supplemental oxygen)

- Includes patients pending discharge due to non-medical or administrative reasons

2: Non-ICU hospital ward (or “ready for hospital ward”), not requiring supplemental oxygen

- - Includes patients in ICU for administrative/non-medical reasons, who don’t require ICU setting and supplemental oxygen

3: Non-ICU hospital ward (or “ready for hospital ward”), requiring supplemental oxygen

- - Includes patients in ICU for administrative/non-medical reasons, who don’t require ICU setting, but require supplemental oxygen

4: ICU or non-ICU hospital ward, requiring non-invasive ventilation or high-flow oxygen

- - Includes patients requiring ICU care, but waiting for ICU setting
  - Includes patients in ICU for administrative/non-medical reasons, who don’t require ICU setting, but require non-invasive ventilation or high-flow oxygen

5: ICU, requiring intubation and mechanical ventilation

6: ICU, requiring extracorporeal membrane oxygenation (ECMO) or mechanical ventilation and additional organ support (e.g., vasopressors, renal replacement therapy)

7: Death

1. **Vital Signs and Oxygenation will be collected as follows:**

- Temperature, blood pressure, respiratory rate, pulse oximeter, oxygenation %, and setting (amount, type)
- To be collected as clinically indicated (due to AEs), in addition to the required time points

1. **Routine labs are as follows:**

- CBC+ diff: WBC count, RBC count, hemoglobin, hematocrit, platelet count, differential count
- Lytes: Bicarbonate, sodium, potassium, chloride, BUN creatinine
- LFT: Total bilirubin, ALP, ALT, and AST
- Ferritin
- CRP
- D-dimers
- Screening only: Pregnancy test for women of childbearing potential

1. **Special labs (stored) are as follows:**

A blood sample of 20ml will be collected and stored for future analysis (i.e., immune profile and cytokine measurements: IL-2, IL-7, granulocyte colony stimulating factor, interferon-γ inducible protein 10, monocyte chemoattractant protein 1, macrophage inflammatory protein 1-α, and tumour necrosis factor-α, ferritin, IL-6, IL-10, IFN- α, IFN- γ).

1. **Radiation Process:**

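### Pregnancies are to be reported for 6 months after LDRT, but the fertility form's agreement stops at 3 months and no contact is scheduled after Day 28

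*Protocol*

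**What the plan says.** Three places in the protocol set a pregnancy-related period.

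- **Case Report Form, Fertility Status Form.** The woman makes one of two commitments. The first reads "patient agrees to remain on birth control throughout the study and for 3 months after the last dose". The second is abstinence, for the same 3-month period.
- **Exclusion Criteria, item 5.** Not eligible: "Pregnant and/or planned to be pregnant within in next 6 months".
- **Adverse Events.** "Pregnancy reporting will begin with first dose of LDRT through 6 months post-dose".

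The follow-up against which these must be read is short.

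- **Synopsis.** Participant duration is "28d from enrollment"; the overall study duration is given as 3 months.
- **End of study definition.** "Observation period for the study will end on day 28 or at the time of discharge (or death), whichever comes first".
- **Study Procedures, Discharge.** "If participant is discharged prior to Day 14, then monitoring for safety (Adverse Events, Concomitant Medications) will continue through Day 14". Table 1 and the Day 14 procedures say the same and allow a phone call.
- **Routine labs.** "Screening only: Pregnancy test for women of childbearing potential".

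Table 1 has no column after Day 28 other than discharge. LDRT is a single dose on Day 1, so the form's last dose and the reporting rule's first dose are the same event.

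**The concern.** The protocol commits to six months of pregnancy reporting, and its visit schedule contains nothing that would produce the reports. The only precaution agreement visible in the document covers half of that period, and the document does not say why the two differ.

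The stake is safety ascertainment. Congenital anomaly in a child born to an exposed mother is one of the protocol's own criteria for a serious adverse event, and the Serious Adverse Event Form has a box for pregnancy. The protocol therefore means to collect this information. The women who could conceive in the window are largely those who recover and go home, and they have the shortest scheduled contact. If the final report states that no pregnancies occurred, the reader could not tell whether there were none or whether none came to the site's attention.

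**Working it through.** The protocol gives no calculation on this point, so there is no figure to reproduce. The check sets the stated windows on one time axis, with the Day 1 dose as day 0 and one month taken as 365.25 / 12 = 30.44 days.

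**Length of each window**

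- Reporting: 6 × 30.44 = 182.6, about 183 days after the dose.
- Contraception or abstinence agreement: 3 × 30.44 = 91.3, about 91 days after the dose.
- Exclusion 5: 6 months from entry. LDRT is to follow within 48 hours of eligibility and enrolment, so this ends at nearly the same point as the reporting window.
- Latest scheduled contact: Day 28, which is 28 − 1 = 27 days after the dose.
- Latest required contact after discharge before Day 14: Day 14, which is 14 − 1 = 13 days after the dose.

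**Agreement against reporting**

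- 182.6 − 91.3 = 91.3, about 91 days (months 4 to 6) inside the reporting window but after the agreement has ended.
- Reading the form's words about the whole study as the 3-month overall duration does not extend this. A woman dosed within that period would still be released no later than about 3 months after her dose.
- Exclusion 5 covers planned pregnancy only. The inclusion and exclusion lists contain no contraception requirement. What no agreement covers is therefore unplanned pregnancy in months 4 to 6.

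**Scheduled contact against reporting**

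- Best case, still in hospital at Day 28: 27 / 183 = 15% of the window has planned contact; 183 − 27 = 156 days have none, and 156 / 30.44 = 5.1 months.
- Discharge before Day 14: 13 / 183 = 7% has required contact; 183 − 13 = 170 days have none, and 170 / 30.44 = 5.6 months.
- Discharge between Day 14 and Day 28: contact ends at discharge, so the result lies between these two.

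**Study duration against reporting**

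- If the 3-month study duration is counted from the first enrolment (an assumption; the Synopsis does not say), even the first participant's 6-month window runs about 6 − 3 = 3 months past the end of the study. Later participants' windows run further.
- The closeout report falls due at the end of the approved duration or on completion of activities, whichever is first. It could therefore be filed before any participant's reporting window has closed.

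**The case against.** The best reply is that the three passages govern different things: a precaution agreement, a question about intention at entry, and a reporting period. A site can comply with all three at once, and a reporting period longer than a precaution period is not in itself an error. That stands. The difference between 3 and 6 months is an unexplained mismatch, and it would be too strong to say that the rules cannot be followed together.

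Several stronger conclusions are tempting, and the protocol does not support them.

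- A reader might infer that half of a 6-month risk period is unprotected. No section defines a 6-month risk period; 6 months is a reporting period and an intention criterion. Exclusion 5 also already bars planned pregnancy over that time.
- A reader might infer that pregnancies after Day 28 will go unrecorded. The reporting rule still applies, the Serious Adverse Event Form has a pregnancy option, and safety contact after early discharge already continues past the defined end of observation. A pregnancy that becomes known has a reporting route. What is missing is a scheduled step to learn of one.
- A reader might infer that women are told their precautions end at 3 months. The fertility form is a site record. What participants are told is in the consent forms, which are not in the copy reviewed and may give another period or ask women to notify the site.

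It is also fair to say that the numbers affected are small. At most 20 participants are enrolled, the number of women of childbearing potential is not given, and the protocol cites mortality of 50-80% among ventilated patients. This limits the weight of the point but does not give the reporting rule a means of execution.

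**Conclusion.** The point holds as a gap between a commitment and its schedule, together with an unexplained mismatch of periods. At least about 156 of 183 reporting days (85%) have no scheduled contact, rising to about 170 (93%) for a woman discharged before Day 14. No precaution agreement covers unplanned pregnancy in about the last 91 days of the window.

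This rests on three assumptions: that the single dose on Day 1 starts every window, that Table 1 and Study Procedures list all planned contacts, and that the consent forms add no later contact. The last cannot be checked here. Further wording in the consent forms could supply a contact, but it would not remove the difference between the fertility form and the other two sections.

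The consequence is confined to long-term safety ascertainment. The 24-hour primary endpoints, the efficacy endpoints, the sample size and the halting rule do not depend on it. It should be corrected, but it does not threaten the trial's main conclusions.

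**What to change.** The sponsor and investigators should reconcile the Fertility Status Form, exclusion criterion 5 and the pregnancy-reporting sentence in Adverse Events with each other. They should also reconcile them with the Synopsis durations, Table 1, the End of study definition and the Discharge procedures, and check the consent forms against the result. If the periods are meant to differ, a sentence should say why. The choice of duration is theirs; this review does not propose one.

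Then one of two changes is needed.

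1. Add one phone contact to Table 1 and Study Procedures for women of childbearing potential at the end of the reporting window, and state that follow-up for this purpose outlasts Day 28 and the 3-month study duration.
2. Restate the reporting commitment to match the period actually followed, and say in the report that later pregnancies were not sought.

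A call at the end of the window would find pregnancies but not the outcome of those still continuing. If outcomes are wanted, the text should say how a known pregnancy is followed.

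The cost is a wording amendment to the protocol and form, with ethics and regulatory approval as for any amendment, and under the first option between 0 and 20 calls in total.
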